**Table 1. Monthly patient inclusion per center in a stepped wedge design.**

| Period | Center 1                      | Center 2   | Center 3   | Center 4   | Center 5   | Center 6   | Center 7   | Center 8   | Center 9   | Center 10  | Total |            |
|--------|-------------------------------|------------|------------|------------|------------|------------|------------|------------|------------|------------|-------|------------|
|        | Anticipated included patients |            |            |            |            |            |            |            |            |            |       | Cumulative |
| Jul-25 | 4                             | 4          | 4          | 4          | 4          | 4          | 4          | 4          | 4          | 4          | 40    | 40         |
| Aug-25 | 6                             | 6          | 6          | 6          | 6          | 6          | 6          | 6          | 6          | 6          | 60    | 100        |
| Sep-25 | 10                            | 10         | 10         | 10         | 10         | 10         | 10         | 10         | 10         | 10         | 100   | 200        |
| Oct-25 | 10                            | 10         | 10         | 10         | 10         | 10         | 10         | 10         | 10         | 10         | 100   | 300        |
| Nov-25 | Transition                    | Transition | 10         | 10         | 10         | 10         | 10         | 10         | 10         | 10         | 80    | 380        |
| Dec-25 | Transition                    | Transition | Transition | Transition | 10         | 10         | 10         | 10         | 10         | 10         | 60    | 440        |
| Jan-26 | 10                            | 10         | Transition | Transition | Transition | Transition | 10         | 10         | 10         | 10         | 60    | 500        |
| Feb-26 | 10                            | 10         | 10         | 10         | Transition | Transition | Transition | Transition | 10         | 10         | 60    | 560        |
| Mar-26 | 10                            | 10         | 10         | 10         | 10         | 10         | Transition | Transition | Transition | Transition | 60    | 620        |
| Apr-26 | 10                            | 10         | 10         | 10         | 10         | 10         | 10         | 10         | Transition | Transition | 80    | 700        |
| May-26 | 10                            | 10         | 10         | 10         | 10         | 10         | 10         | 10         | 10         | 10         | 100   | 800        |
| Jun-26 | 10                            | 10         | 10         | 10         | 10         | 10         | 10         | 10         | 10         | 10         | 100   | 900        |
| Jul-26 | 6                             | 6          | 6          | 6          | 6          | 6          | 6          | 6          | 6          | 6          | 60    | 960        |
| Aug-26 | 4                             | 4          | 4          | 4          | 4          | 4          | 4          | 4          | 4          | 4          | 40    | 1000       |
| Total  | 100                           | 100        | 100        | 100        | 100        | 100        | 100        | 100        | 100        | 100        | 1000  |            |

|                          |
|--------------------------|
| Routine follow-up (RFU)  |
| Check-Up On Demand (COD) |

**Note:** The numbers per month represent the inclusion of patients with either THA or TKA, starting with 2 patients per month for each surgery, followed by 3 patients per month, and then 5 patients with THA and 5 patients with TKA per month.

The order in which the ten hospitals transition from RFU to COD will be determined through randomization. Randomization at the center level enhances the study's methodological rigor, reducing potential biases and increasing the generalizability and strength of the evidence. Besides, the study will be nested in the LROI database, which facilitates long term FU to monitor revision surgeries and mortality beyond the current projects timeline, with minimal additional effort.

## 4. STUDY POPULATION

### 4.1 Population (base)

The study population will consist of patients scheduled for primary Total Hip Arthroplasty (THA) or Total Knee Arthroplasty (TKA) due to osteoarthritis within the Netherlands. This population is drawn from a diverse source population, reflecting the broader demographic characteristics of patients undergoing these procedures in Dutch hospitals.

Patients undergoing THA and TKA are predominantly female, with more than 60% representation for both procedures. The average age of patients is approximately 70 years for THA and 68 years for TKA.

On average, each participating center performs 600 THA and 400 TKA procedures annually.

Given that, there is a high likelihood that the planned recruitment targets will be met. Additionally, the intervention is part of standard care regardless of whether the patient participates in the study, and the study burden for participants is minimal, further increasing the probability of successful recruitment.

### **4.2 Inclusion criteria**

In order to be eligible to participate in this study, a participant must meet all of the following criteria:

- Painful and disabled hip or knee joint resulting from osteoarthritis
- Scheduled for primary THA or TKA surgery
- Age 50 years or older at the time of THA or TKA
- Capable and willing to complete questionnaires
- Proficient in Dutch or English
- Willing to provide informed consent

### **4.3 Exclusion criteria**

A potential participant who meets any of the following criteria will be excluded from participation in this study:

- Other indication for surgery than osteoarthritis
- Scheduled for hip or knee revision arthroplasty, except a conversion from unicompartmental knee arthroplasty to TKA or from hip hemiarthroplasty/resurfacing to THA
- Already participating in this study due to a previous hip or knee surgery

### **4.4 Sample size calculation**

We carefully considered the number of patients needed to obtain reliable estimates of the outcomes with the co-creating stakeholders and also asked orthopaedic surgeons for their opinion of convincing evidence. The agreed sample size is 250 patients per group. To provide a rough indication of the statistical power, we used the online power calculator tool available on Sealed Envelope (18). If there is truly no difference between COD and RFU, 190 patients (per intervention group) are required to be 90% sure that the lower limit of a one-sided 97.5% confidence interval will be above the non-inferiority limit of 3 on the PROMIS score with a standard deviation of 9. Anticipating 20-25% loss to follow up, we will include 250 patients per study intervention group (RFU and COD), thus a total of 500 THA and 500 TKA patients.

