Despite this, eliminating RFU entirely is not without risks. The balance between reducing unnecessary healthcare resource use and ensuring patient safety requires careful consideration. Additionally, patients may find it reassuring to receive confirmation that everything is going well and that they can go back to normal activities, especially as many are not fully recovered at the clinical visit within 3 months post-surgery. Therefore, we suggest a final follow-up within 3 months and then offering COD, as requested by the patient or the healthcare provider (HCP).

The primary objective of this study is to assess whether RFU after THA and TKA can be safely replaced by COD, by comparing the cost-effectiveness of the two approaches 1 year after surgery. The HAKA trial will generate the high-quality evidence necessary to standardize care and guide future clinical practice.

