## **8.3 Study procedures**

Patients scheduled for total THA or TKA will be invited to participate in the study prior to their surgery. This timing ensures that participation is not influenced by the surgery itself, and a patient's potential preference for follow-up care.

Information on patient background will be collected to explore potential differences in follow-up needs, including among patients with different ethnic backgrounds. Previous research shows that people with a migrant background visit specialists and hospitals less often than

native Dutch patients with similar health and SES (19). Acknowledging the sensitivity of this topic, a 'prefer not to say' option is provided.

If the center where the patient undergoes surgery is in RFU phase, follow-up visits will be scheduled within 3 months and 1 year postoperatively. If the center is in the COD phase, patients will receive instructions during their 3-month follow-up on when and how to contact a HCP in case of concerns or complaints. In the COD phase, no standard 1-year follow-up visit will be scheduled.

Participants will be followed up to 2 years after surgery, i.e. 1 year after RFU or COD. The primary outcome, costs and the EQ-5D-5L will be measured pre-operative, at 1 year after surgery and at 15, 18 and 24 months after surgery. The other outcomes will be measured pre-operative (baseline) and at 1 year and 2 years after surgery (endpoint). Figure 1 depicts a flowchart of study participation.

[figure not shown]

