### **10.1 Primary study parameter(s)**

PROMIS physical function will be presented as mean with standard deviation, assuming normality. Differences in PROMIS physical function between the RFU and COD groups will be compared using linear mixed models, with repeated measurements clustered within participants and participants clustered within hospitals (random intercepts). The intervention group (RFU vs. COD), baseline PROMIS physical function, and time points (12, 15, 18 and 24) will be included as fixed effects to determine the crude effect of the intervention at each time point, with the primary outcome at 24 months. Given the stepped wedge design, the duration of the intervention period differs between sites. Therefore “period” is also included as a fixed effect. To assess of the effect of COD might increase over a longer period of time, an interaction term (period \* intervention) will be tested for these possible time effects for the primary outcome.

For healthcare consumption, the percentage of patients who have had at least one clinical visit or X-ray 1 year after RFU or COD will be presented for each group. Additionally, the average number of visits and X-rays per patient will be reported.

A logistic generalized linear mixed model (GLMM) will be used to compare the presence or absence of visits/X-rays (yes/no per patient) between RFU and COD. A Poisson regression analysis will be performed to assess the average number of visits and X-rays per patient, adjusting for potential confounders. Interaction terms between the confounders and the intervention group will also be included to explore whether certain patient characteristics influence the differences in healthcare consumption between RFU and COD.

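### The non-inferiority limit in section 4.4 has no sign or direction, and the primary analysis in section 10.1 never uses it

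*Protocol*

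**What the plan says.** Protocol section 1 poses a replacement question: the trial is to "assess whether RFU after THA and TKA can be safely replaced by COD". Section 2 puts the primary objective neutrally, asking for the effect of COD compared with RFU on physical function at 2 years, and does not mention non-inferiority.

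Section 4.4 is the only place where non-inferiority appears. Its criterion reads: "the lower limit of a one-sided 97.5% confidence interval will be above the non-inferiority limit of 3 on the PROMIS score". The other inputs are equal true means, an SD of 9 and 90% power, and the result is 190 patients in each group. The section describes this as a rough indication of power and raises 190 to 250 per group for 20-25% loss to follow-up. It does not say which group is subtracted from which.

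Section 10.1 gives the primary analysis: "Differences in PROMIS physical function between the RFU and COD groups will be compared using linear mixed models". The model has random intercepts for participant and hospital, and fixed effects for group, baseline score, time point and period. The primary contrast is at 24 months. The section mentions no margin, no confidence limit and no rule for reaching a conclusion.

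Section 8.3 says whether higher or lower is better for EQ-5D-5L, pain and satisfaction. For PROMIS it gives only the scaling (mean 50, SD 10).

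**The concern.** A non-inferiority conclusion needs four things: a contrast with a direction, a scale with a direction, a signed margin, and a rule linking the analysis to that margin. The protocol gives the size of the margin and the confidence level, but leaves the contrast and scale direction unstated. It prints a limit that does not fit its own power statement, and it describes a primary analysis that does not refer to the margin.

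At stake is how the 24-month result will be read. The trial is meant to support ending a guideline-recommended visit. With no margin rule beside the mixed model, an estimate with a wide interval and a non-significant p-value could be reported as showing no difference, although its interval reaches well below a 3-point deficit.

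**Working it through.** Inputs, all from section 4.4: limit 3, SD 9, true difference 0, one-sided 97.5% confidence limit, 90% power, 190 analysed per group. A normal approximation is used throughout. Higher PROMIS is taken as better, which is an assumption because section 8.3 does not say so.

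1. **Reproducing the plan's figure.** n = 2 × [SD × (z0.975 + z0.90) / margin]² = 2 × [9 × (1.960 + 1.282) / 3]² = 189.1, rounded up to 190. The stated number reproduces exactly. A two-sided 5% test for a 3-point difference with 90% power also gives 190, so the number alone does not show which framework was meant. The non-inferiority wording and the premise of no true difference do.

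2. **Planned precision.** SE = 9 × √(2/190) = 0.923. Half-width of the two-sided 95% interval = 1.96 × 0.923 = 1.81. The lower limit of that interval is the one-sided 97.5% lower limit.

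3. **The limit read literally as 3.** The lower limit exceeds 3 only if the estimate exceeds 3 + 1.81 = 4.81. With true difference 0, P = P(Z > 4.81/0.923) = P(Z > 5.21) = 9.5e-8, about 1e-7. To reach 90% under this reading, COD would have to be truly better by 3 + 0.923 × (1.960 + 1.282) = 5.99 points.

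4. **The limit read as -3 on COD minus RFU.** The lower limit exceeds -3 if the estimate exceeds -3 + 1.81 = -1.19. With true difference 0, P = P(Z > -1.19/0.923) = 90.1%. This matches the plan.

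5. **Coherent forms of the rule.** With higher scores better, there are two equivalent forms: the lower limit of COD minus RFU above -3, or the upper limit of RFU minus COD below +3. The printed text joins the lower limit of the first to the number of the second.

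6. **What the missing link could cost.** Compare two ways of reading the 24-month result at SE 0.923. Reading A passes COD if the two-sided 5% test is non-significant (estimate between -1.81 and 1.81). Reading B passes COD if the lower limit is above -3 (estimate above -1.19).

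| True COD minus RFU | Passes under A | Passes under B |
|---|---|---|
| -3 | 9.9% | 2.5% |
| -2 | 41.8% | 19.0% |

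At a true deficit of 3, reading B stays at 2.5% whatever the SE, because the true value sits on the limit. Under reading A the pass rate rises as the SE grows, so imprecision favours COD.

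**The case against.** The best defence is that the intention is plain. The sentence in section 4.4 speaks of non-inferiority, of no true difference and of 90% certainty, which fit together only for a 3-point deficit. The sample size is right and stays right when the sign is added. The mixed model yields the 24-month estimate and interval that the decision needs, and finer rules may stand in the statistical analysis plan that section 12.1 names. This stands in part. The sign is an editorial correction, and section 10.1 omits the link to the margin but does not state a conflicting rule. It does not excuse the text, because the only threshold in the protocol contradicts its own power statement, and the primary analysis described there is not connected to the question that set the sample size.

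A reader might infer more than the documents support:

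- **That section 10.1 fixes a superiority test, or that non-significance will be taken as safety.** It states no test threshold or conclusion rule for the group contrast, and no section equates non-significance with safety. Reading A is a risk left open.
- **That the false reassurance is far more frequent than 10% because the stepped-wedge design is less precise than the calculation in section 4.4 assumes.** A larger SE would push it up. However, the protocol gives no intracluster correlation, no correlation with baseline and no width for period, so no specific higher figure can be drawn from it.
- **That RFU visits will be lost, biasing the result towards non-inferiority.** By Table 1 the first RFU inclusions are in July 2025 and the last hospitals start COD in May 2026, so every 1-year RFU visit falls after all ten hospitals have switched. Section 8.3 nevertheless ties scheduling to the phase at surgery: "If the center where the patient undergoes surgery is in RFU phase, follow-up visits will be scheduled within 3 months and 1 year postoperatively". Nothing says these visits will be cancelled, and visits and X-rays are a primary outcome, so non-attendance would be visible.
- **That a per-protocol analysis must agree before non-inferiority is claimed.** Such sets are commonly left to the analysis plan, and one built on attendance selects on behaviour after allocation, which can itself bias the comparison.

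**Conclusion.** The point holds as a defect of statement and linkage. The limit in section 4.4 is wrong as written: met with probability about 1e-7 where the plan states 90%, and consistent with 190 per group only as -3 for COD minus RFU. Section 10.1 does not use the margin, and section 8.3 leaves the PROMIS direction open, so the written primary analysis does not deliver the conclusion for which the trial was sized.

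The consequence is conditional. Only if non-significance were read as safe would a true 3-point deficit pass in about 10% of trials instead of 2.5%. These figures assume the plan's SD of 9, 190 analysed per group, no clustering or period effects, and higher PROMIS as better. The sample size itself is not in error on this point.

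**What to change.** - **Section 4.4:** write the limit as -3 for COD minus RFU.
- **Section 4.4 or 8.3:** state that a higher PROMIS physical function score is better.
- **Section 10.1:** state that, separately for THA and TKA, non-inferiority is concluded only if the lower limit of the two-sided 95% confidence interval for the 24-month COD minus RFU contrast from the mixed model lies above -3, with patients analysed by their hospital's phase at surgery. Add that a non-significant difference is not evidence of non-inferiority.

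A supporting analysis based on adherence to the allocated follow-up is optional and should not be a condition for the claim.

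The cost is wording in these sections, matched in the analysis plan. The 190 per group, the model and the data collection are unchanged.

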## **5. TREATMENT OF RESEARCH PARTICIPANTS**

Routine Follow Up (RFU): X-ray and clinical visit following THA and TKA guidelines within

standard care: within 3 months and at 1 year after surgery. Patients are welcome to contact a HCP (i.e. general practitioner, physical therapist or hospital) in case of pain, concerns or other symptoms associated with their prosthesis at any time. RFU after THA and TKA is part of the guidelines “Totale heupprothese” and “Totale knieprothese” (5,6).

Check-Up on Demand (COD): final clinical visit with X-ray within 3 months and instructions how and when to contact a HCP. Further check-ups are scheduled only on demand (COD) by the patient or HCP. Patients are welcome to contact a HCP (i.e. general practitioner, physical therapist or hospital) in case of pain, concerns or other symptoms at any time (similar to current standard care).

In clinical practice, there is already variability in how follow-up after total hip or knee arthroplasty is conducted. Both RFU and variations of COD are utilized across different hospitals, with the choice of approach sometimes varying between individual orthopedic surgeons. The Dutch Orthopaedic Association (NOV) has confirmed that the interventions evaluated in this study are considered part of standard care.

### **5.1 Investigational product/treatment**

Not applicable.

### **5.2 Use of co-intervention**

Not applicable.

### **5.3 Escape medication**

Not applicable.

## **6. INVESTIGATIONAL PRODUCT**

Not applicable.

## **7. NON-INVESTIGATIONAL PRODUCT**

Not applicable.

## **8. METHODS**

### **8.1 Study parameters/endpoints**

#### **8.1.1**

##### **Main study parameter/endpoint**

- Clinical: PROMIS physical function
- Process (healthcare consumption): number of clinical visits and X-rays

### 8.1.2

#### **Secondary study parameters/endpoints**

- Number and type of complications (e.g. infection, peri-prosthetic fracture, loosening, malalignment or malposition of components, prosthetic wear, dislocation, etc.)
- Number and type of surgical interventions (e.g. DAIR, partial component exchange, revision surgery (full prosthesis replacement), irrigation and debridement (without component retention), etc.)
- Additional healthcare consumption related to THA or TKA FU (e.g. clinical visit, telephone consultations, X-ray, CT scan, MRI scan, laboratory tests, other)
- Health related quality of life (EQ-5D-5L)
- Numeric Pain Rating Scale (NPRS)
- Numeric Satisfaction Rating Scale (NSRS)
- Costs (based on electronic patient records and additional questionnaires, including all visits to healthcare providers outside the hospital)

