### 1. INTRODUCTION AND RATIONALE

Total Hip Arthroplasty (THA) and Total Knee Arthroplasty (TKA) are two of the most common procedures for patients suffering from osteoarthritis and other degenerative joint diseases. These surgeries are highly effective in reducing pain and improving mobility. In 2022, more than 36,700 THAs and 26,700 TKAs were implanted (1,2), with osteoarthritis being the primary indication in 86% and 97% of cases, respectively (3,4). Given the growing elderly population and rising demand for these surgeries, the need for optimized follow up care has become increasingly important.

Current clinical guidelines recommend routine follow up (RFU) for patients after THA and TKA, with an X-ray and clinical visit within 3 months post-surgery and again at 1 year (5,6). There is currently insufficient high-level evidence to support or challenge the continued use of routine follow-up. The current guidelines for RFU after THA and TKA are based on limited observational data, and randomized controlled trials (RCTs) in this area are rare. A recent NIHR report recommended eliminating RFU before 1 and 10 years in patients with well-functioning implants but did not address the cost-effectiveness or other outcomes relevant to patients associated with RFU 1 year after surgery (7).

Studies show that early follow-up up (FU) to 1 year after surgery results in 0–4.6% detected abnormalities (8,9), of which only a small proportion impacts clinical decision-making and requires additional treatment (10-13). Moreover, in patients indicated for revision surgery, >96.7% present with clinical symptoms such as pain or loss of function. This suggests that early RFU could be safely replaced by check-ups on demand (COD). Registry data also indicate that revisions are rare and typically preceded by symptoms (14-16), bringing the added value of routine follow-up into doubt. Clinical experience further supports the notion that the risk of missed complications is low for asymptomatic patients, which raises the question of whether RFU can be safely de-implemented.

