#### **9.2.2**

##### **Serious adverse events (SAEs)**

A serious adverse event is any untoward medical occurrence or effect that

- results in death;
- is life threatening (at the time of the event);
- requires hospitalisation or prolongation of existing inpatients' hospitalisation;
- results in persistent or significant disability or incapacity;
- is a congenital anomaly or birth defect; or
- any other important medical event that did not result in any of the outcomes listed above due to medical or surgical intervention but could have been based upon appropriate judgement by the investigator.

Only events that are related to the study procedures (RFU or COD) will be considered as serious adverse events. An elective hospital admission will not be considered as a serious adverse event.

Due to the low risk of the interventions (COD or RFU), which are both already part of standard care, hardly any SAEs are to be expected. This means all (S)AEs related to

participation in this study protocol, meaning from COD and RFU, will not be reported to the METC, as no patient benefit is expected from this.

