### **10.2 Secondary study parameter(s)**

For complications, surgical interventions, and additional healthcare consumption, the percentage of patients who have experienced each will be presented for each group.

Additionally, the total number of complications, interventions, and additional healthcare consumption per patient will be reported. Logistic GLMM will be used to compare the presence or absence of complications, surgical interventions, and additional healthcare consumption (yes/no per patient) between RFU and COD. A Poisson regression analysis will be performed to assess the total number of complications, interventions, and additional healthcare consumption per patient, adjusting for potential confounders.

Quality of life (EQ-5D-5L) and pain (NPRS) will be analysed using mixed models, with repeated measures clustered within participants and participants within hospitals (random intercepts). Intervention group (RFU vs. active COD vs. passive COD), baseline score, and time (15, 18 and 24 months) are included as fixed effects. Satisfaction (NSRS) will be analyzed using independent t test to compare the mean difference between the RFU and COD group.

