### **12.4 Annual progress report**

The sponsor/investigator will submit a summary of the progress of the trial to the review committee once a year. Information will be provided on the date of inclusion of the first participant, numbers of participants included and numbers of participants that have completed the trial, serious adverse events, other problems, and amendments.

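### Complications are compared as recorded although only RFU patients have a scheduled 1-year X-ray, and the window is undefined, so the comparison can be biased by detection in either direction

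*Protocol*

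**What the plan says.** **Follow-up.** Sections 5 and 8.3 and Table 2 give both arms a visit and X-ray within 3 months. Only RFU has a scheduled visit and X-ray at 1 year; afterwards COD patients are seen only on request.

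**Endpoint and analysis.** Section 8.1.2 lists "Number and type of complications (e.g. infection, peri-prosthetic fracture, loosening, malalignment or malposition of components, prosthetic wear, dislocation, etc". Section 10.2 states: "Logistic GLMM will be used to compare the presence or absence of complications, surgical interventions, and additional healthcare consumption (yes/no per patient". A Poisson model for the total number follows. The protocol text gives no split by symptoms or by how the event was found.

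**Window.** Section 8.1.3 lists complications from surgery to one year as a separate, other parameter. Section 8.3 describes the 2-year endpoint as one year after RFU or COD. A finding made at the 1-year RFU visit sits on that boundary, and no rule assigns it to a side.

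**Expected yield.** Section 1 puts abnormalities detected at early follow-up, up to 1 year, at 0-4.6%, "of which only a small proportion impacts clinical decision-making and requires additional treatment". It adds that more than 96.7% of patients indicated for revision have symptoms.

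**Collection and reporting.** Table 2 marks complications at 24 months only, whereas section 8.3 has outcomes other than PROMIS, costs and EQ-5D-5L measured at 1 and 2 years. Section 9.2.2 says that related (S)AEs "will not be reported to the METC, as no patient benefit is expected from this". Section 12.4 says that the yearly report to the review committee covers "numbers of participants included and numbers of participants that have completed the trial, serious adverse events, other problems, and amendments".

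**The concern.** The Summary names missed complications as a risk of COD, and section 11.4 accepts that problems without symptoms may not lead a patient to seek contact. The planned comparison cannot show that harm directly. A loosening or malposition that is present but not imaged under COD is scored as absent, while the same finding at a routine RFU X-ray is scored as present. The strategy under test changes the chance that the outcome is recorded, and neither a larger sample nor covariate adjustment removes this.

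The open window makes it worse, because the reader cannot tell which way the bias runs. At stake is the interpretation of the complication comparison, not the PROMIS comparison.

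**Working it through.** **1. Group size.** The only sample-size figure is for PROMIS: "190 patients (per intervention group) are required to be 90% sure", with a margin of 3 "on the PROMIS score with a standard deviation of 9". Check: n = 2 × (1.960 + 1.282)² × 9² / 3² = 189.1, so 190 per group. With 24% loss, 190 / 0.76 = 250, inside the stated 20-25%. Table 1 gives 500 RFU inclusions (40+60+100+100+80+60+40+20) and 500 COD inclusions (20+40+60+80+100+100+60+40) over both joints, hence 250 per arm per joint. Nothing is sized for complications.

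**2. If 1-year visit findings count in the endpoint.** Let p be the complication rate recorded alike in both arms and a the extra share recorded only because of the routine visit. The protocol gives no p, so 3% and 4% are assumptions. The range for a is 0-4.6% (section 1), used as an upper bound.

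- Extra RFU cases = 250 × a.
- COD:RFU odds ratio with no true difference = [p/(1−p)] / [(p+a)/(1−p−a)].
- Example: p = 3%, a = 4.6%: (0.03/0.97) / (0.076/0.924) = 0.0309 / 0.0823 = 0.38.

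| a | extra RFU cases per 250 | odds ratio, p = 3% | odds ratio, p = 4% | chance of false significance favouring COD, p = 4% |
|---|---|---|---|---|
| 0% | 0 | 1.00 | 1.00 | 2.5% (nominal) |
| 1% | 2.5 | 0.74 | 0.79 | 8% |
| 2.3% | 5.8 | 0.55 | 0.62 | 21% |
| 4.6% | 11.5 | 0.38 | 0.44 | 56% |

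The last column is for a two-sided 5% comparison of two proportions with 250 per arm, ignoring clustering and period, so it is indicative only. At a = 4.6% it is 72% for p = 2%, 46% for p = 6%, and 45% for p = 4% with 190 evaluable patients per arm.

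Masking works the same way: observed COD minus RFU = true excess − a. A true COD excess of 2 points shows as 2.0 − 2.3 = −0.3 points at a = 2.3%, and an excess of 4.6 points disappears at the upper bound.

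**3. If 1-year visit findings fall in the earlier parameter.** They leave the later window for RFU, while under COD some of the same problems surface in the second year. Take p = 4% and a = 2.3%, and assume that half would surface later. RFU becomes 4.0 − 0.5 × 2.3 = 2.85% against 4.0% for COD, an odds ratio of (0.04/0.96) / (0.0285/0.9715) = 1.42. The direction reverses.

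**4. Timing.** COD inclusions in Table 1 run from January to August 2026. Taking surgery as close to inclusion, the omitted 1-year visits fall from about January to August 2027. The first 24-month record of a COD patient comes about January 2028, about 5 months after the last omitted visit.

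**The case against.** **The size may be negligible.** The protocol's range starts at 0%. The 4.6% counts abnormalities rather than recordable complications, may include findings at the within-3-month visit that both arms have, and includes patients with symptoms who could also present under COD. If the share without symptoms among revision patients (below 3.3%) held for all complications, the difference would be 250 × 0.04 × 0.033 = 0.33 case at a 4% base rate, and under 0.5 at 6%. This stands as a reason to treat 11.5 as a ceiling. It does not settle the matter, because the symptom figure concerns patients indicated for revision and not the wider list in section 8.1.2.

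**Other outcomes depend less on detection.** Surgical interventions are already compared, revisions also come from the LROI register, and pain, function and quality of life may show the consequences of a missed problem. This stands and limits the damage.

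**Stronger readings that a reader might infer.** One is that RFU will show more complications and COD will look safer. The 0% lower end and the separate parameter in section 8.1.3 rule out that certainty. Another is that nothing could be acted on during the trial. Section 9.2.1 keeps adverse-event reporting for events directly linked to the presence or absence of the 1-year visit, and section 9.1 lets the sponsor suspend the study. That route is limited, since complications are otherwise exempt from separate reporting, but it exists. A third is that this is the trial's main safety comparison; the protocol designates none.

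**Mode of detection could be left to a SAP.** In part, yes. But it can be analysed only if it is recorded, and the boundary between 8.1.2 and 8.1.3 is set in the protocol.

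**Conclusion.** The concern holds in a conditional form. Ascertainment is unequal by design, complications are compared as recorded, and the window is not fixed, so the comparison can be biased by detection. If 1-year visit findings count, the bias is towards COD and amounts to at most 0 to 11.5 extra RFU cases per 250 per joint (odds ratio 1.00 to 0.38 at an assumed 3% base rate with no true difference). If they do not count, the bias may run against COD. The base rates and the share surfacing later are assumptions, and 4.6% is a ceiling rather than an expected value.

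Two contradictions are real but separate from the bias: Table 2 against section 8.3 on when complications are collected, and section 9.2.2 against section 12.4 on SAE reporting. The change should be made; PROMIS is unaffected.

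**What to change.** 1. State one complication window that applies alike to both arms, and say where findings at the 1-year RFU visit fall relative to the parameter in section 8.1.3.
2. Add two eCRF fields per complication: how it was detected, and whether it was treated.
3. Base the between-arm safety comparison on symptomatic or treated complications, read together with surgical interventions and LROI revisions.
4. Report findings seen only on routine imaging separately, as the yield of RFU.
5. Reconcile Table 2 with section 8.3 on collection times, and section 9.2.2 with section 12.4 on SAE reporting.

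Cost: two fields, wording changes, and possibly a second record review if collection at 1 year is confirmed. Fewer events remain in the comparison, and judging what is symptomatic will be partly unblinded. Some dependence on detection stays, because a routine visit can itself bring out symptoms or prompt treatment; the restriction reduces the bias but does not remove it.
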